#### Measures

Measures for aim 3 are summarized in Table 3. The provider surveys and in-depth interviews described in Aim 1 will be repeated post-trial to collect follow-up measures to the baseline assessments, capture adaptations to the interventions, and evaluate changes to the implementation context. Attrition will be addressed through surveys administered to additional providers at centers with missing follow-up data.Treatment fidelity: to examine the fidelity of the provider-level intervention component, we will assess provider training attendance and quality using training logs and evaluations. At the patient level, we will assess the receipt of AAA or AAC as reported by the patient, the number of phone counseling sessions completed and content covered, and NRT use in the AAC + NRT arm. Patient baseline and follow-up surveys will assess the receipt of AAA or AAC components, as applicable. The telephone counselors will assess the number of sessions completed and the duration of each session. They will assess NRT use in the AAC + NRT arm in follow-up phone calls and reasons for non-adherence using the Medication Adherence Questionnaire [52], and any potential NRT use not provided by the trial in the AAA and AAC arms. To assess the intervention dose received by patients, each component will be scored 0 if the full dose is not received and 1 if received (e.g., did not complete/completed each counseling session). A fidelity score will be calculated by summing the individual dose scores (range 0–3). In addition, research assistants will observe a random sample of the phone counseling sessions and document the delivery of essential components of the counseling intervention using the Motivational Interviewing Treatment Integrity coding manual [53]. Observations will be reviewed with the phone counselors to ensure high fidelity.Adaptations: follow-up interviews with the medical director and nurses most involved with the implementation process will include an assessment of adaptations using the Framework for Reporting Adaptations and Modifications-Enhanced (FRAME), a checklist and coding system for reporting adaptations and modifications made to evidence-based interventions [54, 55]. Interviews will assess the following domains related to adaptation, with follow-up open-ended questions in the interviews, as needed: (1) when and how in the implementation process the modification was made; (2) whether the modification was planned/proactive or unplanned/reactive; (3) who determined that the modification should be made; (4) what was modified; (5) at what level of delivery the modification was made (i.e., patient, provider, center); (6) the type or nature of context-level modifications; (7) the extent to which the modification was fidelity-consistent; and (8) reasons for the modification, including (a) the intent or goal of the modification and (b) the contextual factors that influenced the decision. A binary measure will be created for each center to indicate whether adaptations were reported.Sustainability capacity: follow-up provider surveys will assess sustainability capacity using the clinical sustainability assessment tool (CSAT) [56], which measures the organizational factors hypothesized to impact the implementation and sustainability of evidence-based interventions. The CSAT was designed for clinical settings with 35 statements nested into 7 domains: engaged staff/leadership, engaged stakeholders, monitoring/evaluation, planning/implementation, outcomes/effectiveness, workflow integration, and organizational context/ capacity [56].Implementation context and outcomes: the follow-up interviews with the medical director or chief nurse *(n* = 24) will involve the assessment of multi-level barriers and facilitators to implementation and sustainability, organized according to the EPIS framework into the outer setting (e.g., system resources, policies), inner setting (clinic priorities, care climate), and provider (e.g., attitudes towards the intervention), as well as Proctor framework implementation outcomes of acceptability, appropriateness, and sustainability. Similar in-depth interviews will be conducted with MoPH administrators (*n* = 5)—e.g., Director General, Director of the National Tobacco Control Program, Director of Information Technology.

**Table 3 Tab3:** Aim 3 evaluation

	Measures	Instrument/data source	Timing
Fidelity	Provider training attendance and quality	Training log/evaluations	Pre-trial
	Patients received Ask, Advise, Assist or Ask, Advise, Connect	Patient surveys	0, 1 month
	Counseling sessions completed, content	Phone log/checklist	Weeks 1–8
	Patient used 4-week NRT. Fidelity score, sum 2–4 (range 0–3)	Patient log	1 month
Adaptations	Timing, planning level, decision maker, modification, delivery level, context, content, fidelity, reason. Adaptation occurred (0/1)	Provider interviews and surveys	Pre-/post-trial
Sustainability capacity	Staff and leadership, stakeholders, monitoring/evaluation, planning/implementation, outcomes/effectiveness, workflow integration, organizational context/capacity. Overall score (range 1.0–7.0)	Provider surveys	Pre-/post-trial
Implementation context and outcomes	Outer setting (system resources, policies), inner setting (clinic priority, climate), provider (attitudes, knowledge, self-efficacy), implementation outcomes (acceptability, appropriateness)	Health admin. interviews	Post-trial
		Provider interviews and surveys	Pre-/post-trial

*NRT* Nicotine replacement therapy

#### Analysis

We will use an explanatory sequential mixed methods approach [28] to identify the multi-level determinants of implementation and sustainability according to EPIS [17] and Proctor’s framework for implementation outcomes [19]. Our approach will follow an expansion function (with the qualitative interviews helping to expand on quantitative survey findings) and a complementarity function (with the interviews providing context around the variability observed in surveys) [57]. Given the small sample of centers and providers, we will use descriptive statistics to summarize the quantitative data from the pre- and post-trial surveys to assess provider- and center-level measures. To examine the effects of fidelity, each of the individual measures will be analyzed using the univariate GLMM approach as described for aim 2, using logit link function for the binary outcome to evaluate the effect of the interventions. Then, multivariate GLMM will be fitted for the four measures while accounting for the correlations among the measurements within the same subject. Adaptation and sustainability capacity scores will be summarized with descriptive statistics and box plots by center and arm.

Qualitative data collected from in-depth interviews with primary healthcare providers and MoPH administrators will provide additional context to patient and provider survey responses. Given that we will have collected quantitative data before qualitative data, if there are findings that necessitate explanation, we will use the qualitative interviews to explain and expand on quantitative results. Similar to aim 1, qualitative data from the audio recordings of interviews will be transcribed verbatim in Arabic and translated into English. Similarly, interview transcripts will be reviewed using the content, framework, and in-depth analysis approaches. For primary healthcare provider interviews, additional stage-by-theme matrices will be developed (for each center individually, and in the aggregate) to understand changes to implementation context between baseline and follow-up. The final product will be a theoretically informed, empirically grounded model of the multi-level factors associated with implementation of the evidence-based tobacco treatment interventions.

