**Fig. 2 Fig2:**
[figure not shown]
Hybrid study design overview

Table 1 presents an overview of the multilevel intervention components by arm. The proposed multi-level intervention addresses barriers to tobacco treatment at the primary healthcare center and provider levels (e.g., lack of training, lack of systems to prompt tobacco treatment) and at the patient level (e.g., nicotine dependence, social norms). To address primary healthcare center- and provider-level barriers, we will implement clinic reminders and train providers and staff on best practices, including documentation of smoking status and referral to tobacco treatment. To address individual-level barriers, all patients will receive educational materials about the harms of smoking and the benefits of cessation, patients in Arms 2 and 3 will receive phone-based counseling, and patients in Arm 3 will receive phone-based counseling and NRT. We will then conduct follow-up surveys and in-depth interviews with providers and health system administrators to identify the multi-level barriers and facilitators to implementing and sustaining tobacco treatment interventions (Aim 3). Data from Aims 1 and 3 will allow us to assess the implementation context longitudinally. This design allows us to explore the clinical infrastructure and resources needed for effective implementation.

**Table 1 Tab1:** Multilevel intervention components by arm

Level	Motivating need/problem	Component	AAA	AAC	AAC + NRT
Clinic	Lack of integration into practice	Electronic reminders	◉	◉	◉
Provider	Insufficient knowledge, self-efficacy	Provider training	◉	◉	◉
Patient	Insufficient knowledge	Educational materials	◉	◉	◉
	Insufficient self-efficacy, motivation	Phone counseling		◉	◉
	Nicotine withdrawal symptoms	Nicotine patches			◉

*AAA* Ask, Advise, Assist, *AAC* Ask, Advise, Connect, *NRT* nicotine replacement therapy

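### The Aim 3 fidelity models compare arms on components that some arms are not offered: as written, no arm contrast for trial NRT and no contrast with AAA for counseling can be estimated

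*Protocol article*

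**What the plan says.** All references are to the protocol article.

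- **Components by arm** (Study design overview and Table 1): "patients in Arms 2 and 3 will receive phone-based counseling, and patients in Arm 3 will receive phone-based counseling and NRT". AAA has reminders, provider training and educational materials only.
- **Scoring** (Approach for Aim 3, Measures): "each component will be scored 0 if the full dose is not received and 1 if received". Then: "A fidelity score will be calculated by summing the individual dose scores (range 0–3").
- **Items in the score** (Table 3): the fidelity block has four rows, namely provider training, AAA/AAC receipt, counseling sessions and NRT use. The last row reads "Patient used 4-week NRT. Fidelity score, sum 2–4 (range 0–3").
- **Receipt of AAA or AAC** is assessed in every arm: "Patient baseline and follow-up surveys will assess the receipt of AAA or AAC components, as applicable".
- **NRT**: use is a fidelity measure in AAC + NRT. NRT obtained outside the trial is recorded in AAA and AAC, but is not said to enter the score.
- **Models** (Approach for Aim 3, Analysis): each individual measure is analysed with the univariate Aim 2 approach, "using logit link function for the binary outcome to evaluate the effect of the interventions". After that, a "multivariate GLMM will be fitted for the four measures while accounting for the correlations among the measurements within the same subject".
- **Aim 2 approach** (Approach for Aim 2, Analysis): mixed models with a random center effect, comparing arms, with pairwise contrasts.

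**The concern.** An arm that is not offered a component has no events on the matching 0/1 item, whatever the quality of delivery. A logit model with arm as the predictor then tries to estimate an odds ratio against a cell that is empty by design. The result says only that the component was not assigned.

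The summed score has a related weakness. It has one common range, but the number of components a patient can receive depends on the arm. A well-delivered AAA center and a partly delivered AAC + NRT center cannot be ranked on it.

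The joint model raises a separate question of what its four measures are. A provider-level training record has no value for an individual patient, so it cannot contribute to a within-patient correlation.

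At stake is whether the fidelity analysis can show which arm was poorly delivered. The Discussion itself names low fidelity as a potential challenge.

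**Working it through.** **1. Score range.** Inputs: three 0/1 items (Table 3, rows 2–4) and the components by arm (Table 1). The stated range reproduces: 3 items × 1 = 3. This takes counseling as a single 0/1 item, as a 0–3 range requires.

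| Arm | Receipt | Counseling | Trial NRT | Maximum | Share of 3 |
|---|---|---|---|---|---|
| AAA | 1 | 0 | 0 | 1 | 33% |
| AAC | 1 | 1 | 0 | 2 | 67% |
| AAC + NRT | 1 | 1 | 1 | 3 | 100% |

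An AAC + NRT patient who misses one component scores 3 − 1 = 2, above an AAA patient who received everything assigned (1).

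**2. Variation below the maximum.** Assume rates of 0.9, 0.6 and 0.5 for receipt, counseling and NRT where offered, independent of each other.

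- Means: AAA 0.9; AAC 0.9 + 0.6 = 1.5; AAC + NRT 0.9 + 0.6 + 0.5 = 2.0.
- SDs, from √Σp(1 − p): 0.30, 0.57 and 0.76.
- With rates 0.7, 0.4 and 0.3: means 0.7, 1.1 and 1.4; SDs 0.46, 0.67 and 0.81.

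The score does vary within arm. Equal adherence to each offered component still gives different means by design.

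**3. Logit contrasts.** Inputs: 240, 480 and 480 patients in AAA, AAC and AAC + NRT, 8 centers per arm, and an ICC of 0.01 (Sample size and power evaluation). The completion rates were assumed: 0.80/0.80/0.85 for receipt, 0.50 and 0.60 for counseling where offered, and 0.50 for NRT where offered. One data set was simulated with these inputs. The logit was fitted by maximum likelihood on arm without a center effect; a center intercept adds no events to an arm that has none.

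| Item | AAA | AAC | AAC + NRT |
|---|---|---|---|
| AAA/AAC receipt | 197/240 | 383/480 | 394/480 |
| Counseling | 0/240 | 237/480 | 314/480 |
| Trial NRT | 0/240 | 0/480 | 239/480 |

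- *Receipt:* both log odds ratios against AAC are 0.15, with SE 0.20 for AAA and 0.16 for AAC + NRT. All contrasts are estimable.
- *Counseling, AAC + NRT versus AAC:* ln[(314/166)/(237/243)] = 0.66; SE = √(1/314 + 1/166 + 1/237 + 1/243) = 0.13. Estimable.
- *Counseling, AAA versus AAC:* the AAA odds are 0/240, so the log odds ratio has no finite maximum. The fitted coefficient was −11.2, −16.2, −21.2 and −26.2 after 10, 15, 20 and 25 iterations, while its SE rose from 10.6 to about 19,170. The contrast of AAA with AAC + NRT has the same empty cell.
- *Trial NRT:* AAA and AAC each diverge in the same way against AAC + NRT. AAA versus AAC compares zero odds with zero odds and is undefined.

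This is quasi-complete separation. The divergence follows from the empty cells, not from the assumed rates. Those rates affect only the finite estimates.

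**4. NRT from outside the trial.** Counting it at an assumed 2% in AAA and AAC makes the NRT model converge (SE about 0.4). The item then records off-protocol use in those arms and is no longer a fidelity measure there.

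**5. The four measures.** Since Table 3 sums rows 2–4, its rows are implicitly numbered, and the natural set of four is its four rows. Row 1, "Provider training attendance and quality", comes from training logs and evaluations before the trial, and the Measures section treats it as provider-level. It has no within-patient value. If the fourth measure is instead the score, it is the exact sum of the other three and adds no information to a joint model.

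**The case against.** The strongest reply has four parts.

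**The measures are already partly tied to arms.** NRT use is described as measured in AAC + NRT, and receipt is assessed as applicable. The Analysis section does not say that every component is modelled in all three arms, and the choice of arms could sit in an analysis plan that is not shown. This has some force. However, the section does fix a model for each individual measure and gives its purpose as evaluating the interventions. Under the Aim 2 approach that is an arm comparison, and for trial NRT no such comparison remains once the model is confined to the arm offered it.

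**The score is a dose score.** The Measures section builds it to describe dose received, and dose should be higher where more is given. That stands. A reader might infer that the plan tests the summed score between arms or reads it as a percentage of 3; the text says neither. The limit is only that a score named for fidelity cannot be compared across arms as fidelity.

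**The four measures are not named.** The patient-level list in Measures can also be counted as four: AAA/AAC receipt, sessions completed, content covered and NRT use. On that reading the within-patient model is coherent. So provider training as the fourth measure is an inference from the row numbering in Table 3, not a statement of the plan.

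**The direction of the model is loosely worded.** The sentence opens by speaking of the effects of fidelity. If fidelity predicted abstinence, the separation argument would not apply. The rest of the sentence, and the joint model that follows, favour the fidelity measures as outcomes.

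**Conclusion.** The point holds in a limited form. As written, trial NRT has no estimable arm contrast and counseling has none involving AAA. The joint model inherits the problem for those contrasts only. The maximum of the score is 1, 2 and 3 by arm, so the raw score reflects dose and cannot rank arms on fidelity. The joint-model sentence does not fit Table 3 on its natural reading and should be corrected or made explicit.

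Two stronger conclusions are tempting and are not supported. One is that the score is fixed by arm: only its ceiling is, and patients vary below it. The other is that the fidelity models as a whole cannot be estimated: AAA/AAC receipt can be compared across all arms, and counseling between AAC and AAC + NRT.

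The conclusion assumes that the fidelity measures are the outcomes, that arm is the predictor, and that NRT obtained outside the trial does not count towards the NRT item. The defect should be corrected because the stated analysis cannot give its result. Its reach is one secondary Aim 3 analysis; the primary outcome, its pairwise comparisons and the sample size are untouched.

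**What to change.** Amend the Aim 3 Analysis section, and the analysis plan to match:

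1. Model AAA/AAC receipt across all three arms.
2. Compare counseling completion between AAC and AAC + NRT only.
3. Report trial NRT use descriptively within AAC + NRT, and NRT obtained outside the trial separately in the other arms.
4. Treat a component that an arm is not offered as not applicable, not as 0, in any model.
5. Name the measures in the joint model, restrict it to patient-level measures in the arms offered them, and leave out the summed score.
6. Summarise provider training by provider and center.
7. Report the score by arm as components received divided by components assigned (denominators 1, 2 and 3), alongside the raw dose score.

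The cost is wording only. All the data are already planned, and neither the sample size nor the primary analysis changes.

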## Discussion

This study addresses a critical need to evaluate the comparative effectiveness and cost-effectiveness of multi-level strategies that integrate smoking cessation into clinical practice in low-resource settings. It builds upon an existing evidence-informed in-person smoking cessation program at a medical center in Beirut, Lebanon, and tailors it to a phone-based counseling intervention to smokers in Lebanon.

Considering the strong evidence that combining behavioral counseling and pharmacotherapy is more effective than either alone [22], that directly connecting smokers to phone-based counseling is more effective than standard referral [58], and that access to NRT in Lebanon and other low-resource settings is often limited [59], we will conduct a group-randomized trial of 24 centers to compare three arms, AAA, AAC, and AAC + NRT.

We expect to encounter a few potential challenges, which we have planned for alternative approaches. We might face difficulties in recruiting centers and patients. The team has tried to minimize this risk by securing buy-in for this project at multiple levels, including from MoPH leadership and medical directors at the centers. The study team is also leveraging a history of successful collaboration with the MoPH and the primary healthcare center network [60–63]. Though we expect to meet our recruitment goal, we will recruit additional centers if we are unable to achieve our desired sample from the initial 24 centers. Low fidelity is another potential challenge. In such case, we will provide booster training sessions for providers and center staff and/or telephone counselors, as needed.

This study is significant for its potential to guide large-scale adoption of tobacco treatment guidelines in the Lebanese primary healthcare network as a model for similar efforts to improve preventive practices in clinical settings across other Eastern Mediterranean countries, other LMICs, and other low-resource settings. Specifically, it addresses an urgent need for research into implementation challenges that limit the impact of evidence-based interventions in low-resource settings to reduce the global burden of cancer. The expanded use of rigorous implementation science methods can also be applied in other LMICs and in low-resource settings.

The study will have a significant public health impact as it is expected to provide a replicable model for population-based tobacco treatment interventions in low-resource settings. Prior research suggests that improving the effectiveness of such interventions requires a multi-level approach that addresses both the context of care and the barriers to behavior change [21, 58, 64, 65].

## Data Availability

No study data have been collected yet. Upon study completion, any datasets used and/or analyzed during the current study will be available from the corresponding author ([name]) on reasonable request.

## Abbreviations

AAA: Ask about tobacco use; Advise to quit; Assist with brief counseling
AAC: Ask about tobacco use; Advise to quit; Connect to phone-based counseling
AUB: American University of Beirut
CEA: Cost-effectiveness analysis
CSAT: Clinical sustainability assessment tool
EMR: Eastern Mediterranean Region
EPIS: Exploration, Preparation, Implementation, Sustainment framework
ERR: Excess relative risk scale
FCTC: Framework Convention on Tobacco Control
FRAME: Framework for Reporting Adaptations and Modifications-Enhanced
GLMM: Generalized linear mixed-effects models
ICER: Incremental cost-effectiveness ratio
IRB: Institutional Review Board
LMICs: Low- and middle-income countries
MAR: Missing-at-random
MoPH: Ministry of Public Health
NRT: Nicotine replacement therapy
StaRI: Standards for Reporting Implementation Studies
WHO: World Health Organization
